## Abstract

**Background:**

Applications of mobile technologies (mHealth) have the potential to reduce health inequalities, give patients more control over their health, and improve health care’s cost-effectiveness. The widespread use of mobile phones offers us a new way to prevent cervical cancer. The objective of the study was to design and develop a mobile phone application (app) that aims to conduct a behavioral intervention for women and to evaluate the efficacy of the app-based intervention.

**Methods:**

This study involves 5 phases. In the first phase, understanding women’s perspectives will be identified using a qualitative approach based on the I-Change model. In phase 2, the results from the qualitative approach and requirement prioritization through providing experts’ perspectives will be done. The main outputs of this phase will be resulted in prioritizing the main measurable effective variables of the I-Change model. Phase 3 will be processed for the development and psychometric of an assessment tool regarding selected constructs. In phase 4, the App framework and content development will be performed. In phase 5, a three-armed, parallel-design randomized controlled trial will be conducted on women. Two hundred ten women will be randomly assigned to three groups including two intervention groups and one control group. The intervention groups included the following: (1) a mobile application and (2) a digital book. The data will be evaluated using tools designed and constructed in phase 3 of the study at baseline in 3-month follow-up assessments. The impact of the two interventions on cervical cancer prevention behaviors through mobile-based educational intervention will then be evaluated.

**Discussion:**

A theory-based health education program using a mobile app to improve cervical cancer-preventive behaviors will be implemented for the first time in Iran. With an effective health mobile-based educational design, it is very important to determine whether Iranian women will be motivated to adhere to preventive behavior related to CC.

**Trial registration:**

Iranian Clinical Trial Register IRCT20181205041861N3. Registered V2.0 on 26 October 2021.

## Background

Cervical cancer is one of the “gravest threats to women’s lives,” according to the World Health Organization (WHO) [1]. Cervical cancer is a major public health issue and the fourth most frequent cancer among women in the world, with an estimated 570,000 new cases diagnosed each year [2]. According to WHO estimates, cervical cancer will cause 474,000 women per year by 2030 [3]. Cervical cancer is a disease of inequality. Women in low- and middle-income nations are disproportionately affected by cervical cancer [4]. The vast majority of cervical cancer deaths (90%) occur in low- and middle-income countries, despite these nations receiving only 5% of global cancer resources [5, 6]. Cervical cancer can be prevented in the majority of cases if women get screened. Significant gaps in access to care, on the other hand, have moved the disease burden to resource-poor countries in Africa, Asia, and Latin America [7]. CC is a disease that affects all women who have had at least one sexual encounter. This disease is slow-moving, and early identification with a Pap smear can avert serious complications [8].

### Cervical cancer status in Iran

In Iran, the rate of cervical cancer is reported to be 3.73 per 100,000 women [9]. While cervical cancer is not frequent in Iran, patients usually seek medical help when the disease has progressed to an advanced stage [10, 11], and the mortality rate is high [12]. Most Iranian women are unaware of screening tests and Pap smears test (PST) because of their cultural, economic, and social status [13]. Despite the remarkable success of the Pap test in detecting cervical cancer, the participation rate in developing countries is only 5%, compared to about 90% in high-income countries such as the USA [14]. Many studies in Iran have reported a low participation rate in this test. For example, this rate has been reported at 27.1% in Babazadeh et al.’s [15] study [16], 50% in Farzaneh et al.’s [16] study, and 58.6% in Ghalavandi et al.’s research in Andimeshk city [17].

### Global prevention strategy for CC

The World Health Organization (WHO) established a global strategy to speed up the elimination of cervical cancer in November 2020. By 2030, the goal is to test 70% of women by the age of 35 (and again by the age of 45) and treat 90% of those with precancerous changes [18]. To achieve this lofty goal, scalable screening and cost-effective treatment technologies will be necessary [19]. The impact of cervical cancer prevention initiatives is determined by two key context-specific factors: (1) women’s access to screening and (2) successful treatment acquisition for women who test positive. Due to geographic and infrastructure constraints, access to both screening and treatment is particularly difficult in some locations [20, 21].

### mHealth: a great potential for health education

In the previous several years, the use of mobile technologies has increased [22]. Mobile health (mHealth) has a lot of potential in many aspects of health, such as promotion and prevention, because of this greater access to technology [23]. The use of mobile health to deliver health services has the potential to eliminate inequities, empower individuals to take charge of their health, and enhance the cost-effectiveness of health care [24, 25, 26]. Mobile applications have become increasingly essential in the delivery of educational content in recent years [27]. Because people carry their phones with them wherever they go, educational interventions may be offered at any time to everyone, with further help available on-demand, wherever and whenever it is required. This opportunity allows a wide spectrum of people to benefit from simple and low-cost initiatives [28]. Mobile phones can be used to send motivational messages, monitoring, and behavior change tools [29, 30]. The smartphone application was effective in sustaining the effects of the educational program for prevention of sexually transmitted infection [31]. To educate women and encourage them to participate in cervical cancer screening, and thus strengthening grass root level primary health provision, could be a popular and culturally appropriate intervention, which needs to be tested. Furthermore, it may contribute to the implementation of the National Cervical Cancer Screening and Prevention policy and ultimately help to reduce cervical cancer mortality in Iran. The health promotion package through mobile application will be a simple, feasible, and effective approach. This paper explains our study protocol aiming to determine the effect of educational intervention via mobile app for empowering women in preventive behavior in cervical cancer.

## Methods

### Aim, design, and outcomes

This practical randomized trial aims to evaluate the effect of an interventional education based on I-Change model via mobile phone application on improving preventive behaviors for cervical cancer among Iranian women. An exploratory sequential mixed-methods design will be used in the study.

### Outcome measures

The initial research questions addressed in this study are “Does the educational intervention based on the I-Change model via mobile app affect CC preventive behaviors among Iranian women?”. To answer this main question, the following primary outcomes are expected:Determining and comparing the effects of an educational intervention designed based on the I-Change model via a mobile app knowledge related to CC prevention in women in the target and control groups before, immediately, and 3 months after the interventions.Determining and comparing the effects of an educational intervention designed based on the I-Change model via a mobile app on information factors related to CC prevention in women in the target and control groups before, immediately, and 3 months after the interventions.Determining and comparing the effects of an educational intervention designed based on the I-Change model via a mobile app motivation to CC prevention in women in the target and control groups before, immediately, and 3 months after the interventions.Determining and comparing the effects of an educational intervention designed based on the I-Change model via a mobile app predisposing factors to CC prevention in women in the target and control groups before, immediately, and 3 months after the interventions.Determining and comparing the effects of an educational intervention designed based on the I-Change model via a mobile app behavioral intention to CC prevention in women in the target and control groups before, immediately, and 3 months after the interventions.Determining and comparing the effects of an educational intervention designed based on the I-Change model via a mobile app action to prevent for CC prevention in women in the target and control groups before, immediately, and 3 months after the interventions.

Consequently, we expect the effect of our educational intervention on preventive action regarding CC among women. To assess the expected secondary outcomes, a self-reported assessment addressing preventive actions (using a condom, doing pap-test and genital examination) will be conducted.

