### Sample size and power calculations

The sample size was determined by the primary objective (comparison of participation in the experiment and control groups, respectively) and women will be allocated in equal numbers to the three randomization groups. Following the study conducted [34], the sample size we require in the quantitative phase to provide sufficient power was calculated as 61 persons for each group. This sample size was calculated to be adequate at an alpha of 0.05 and a power of .80, to test for a difference between the groups. We considered a potential dropout rate of 15%. According to the formula below, we should start with a recruitment target of 70 participants in each group: $${n}_1={n}_2=\frac{\left({s}_1^2+{s}_2^2\right){\left({z}_{1- {\propto }\!\left/ \ {2}\right.}+{z}_{1-\beta}\right)}^2\ }{{\left(\mu {\mu}_2\right)}^{2.}}$$

In line with this approach, a total of 210 women aged 18–49 years will be recruited using the inclusion and exclusion criteria listed in Table 1. Participants will be allocated into three groups (the two intervention groups plus one control group).

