#### Phase 5: analysis of intervention outcomes

To ensure that the data is correctly entered, a double-entry of data will be performed by two different individuals. All data obtained from women will be entered into SPSS software. A code will be defined to identify missing data. The obtained data will be kept strictly confidential and will be stored with secured and restricted access; also, the signed consent will be kept locked. Follow-up data are received using the same questionnaires as used at baseline. The intervention will be evaluated based only on Pap smear completion 3 months after the enrollment and baseline survey. Data will be summarized with descriptive statistics (mean, median, standard deviation, percentiles for numerical variables, frequencies, and percentages for categorical variables). To determine the normality of data, Smirnov and Kolmogorov will be used. Determining the frequency of demographic information in both groups is analyzed using descriptive statistics templates. To analyze the quantitative variables, the independent *t*-test and paired *t*-test are analyzed. To compare the mean score, the quantitative (intra-group) variables of the two groups of the test and control groups before and after the intervention were used as independent samples. To compare the means, the quantitative (inter-group) variables were compared between the two groups of control and test before and after paired *t*-test intervention is used. In the case of non-normalization, the mean score of the quantitative (intra-group) variables in the two groups of the test and control groups is used before and after the intervention in Mann-Whitney. To compare the meanings, the quantitative variables (inter-group) were used in both control and test groups before and after the Wilcoxon test. To determine the relationship between the underlying and dependent variables in the case of normal, the Pierson correlation test is used and the Spearman correlation test will be used to determine the relationship between the underlying and dependent variables in the case of normal. To analyze the qualitative variables, a chi-square test is used to analyze the qualitative variables. The significance level in this study is considered to be 0.5. The information obtained will be used by the related statistical software, including SPSS version 23.

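### Six primary I-Change outcomes are set at two post-intervention occasions, the planned tests use an undated before and after, and no readable text says which occasion decides

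*Protocol article*

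**What the plan says.** The protocol article describes the occasions of the questionnaire scores in three places.

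- **Outcome measures.** After the words "the following primary outcomes are expected" come six outcomes: knowledge, information factors, motivation, predisposing factors, behavioural intention and action. Each is to be compared between target and control groups "before, immediately, and 3 months after the interventions". The phrase is repeated for all six.
- **Abstract, Methods.** "The data will be evaluated using tools designed and constructed in phase 3 of the study at baseline in 3-month follow-up assessments". No immediate assessment is mentioned.
- **Phase 5: analysis of intervention outcomes.** "To analyze the quantitative variables, the independent *t*-test and paired *t*-test are analyzed", with Mann-Whitney and Wilcoxon as the non-normal alternatives. The comparison is described as "variables of the two groups of the test and control groups before and after the intervention were used as independent samples". The after measurement has no date. The only dated statement in the section concerns another outcome and another starting point: "The intervention will be evaluated based only on Pap smear completion 3 months after the enrollment and baseline survey".

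The section on sample size and power ties its 61 per group to no occasion. Table 2 (schedule) and Fig. 1 (flow chart) are not shown in the text available.

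**The concern.** A score taken straight after training and a score taken 3 months later answer different questions. The first largely reflects recall of material just seen; the second shows what lasted. They can disagree, because an early gain can fade.

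The outcome section gives the two occasions equal standing. The analysis section has one unlabelled after slot, which either could fill. If the choice is made once data are available, an immediate gain could be reported as the primary finding while the 3-month comparison is null, or the better of the two could be selected. Testing both at 0.05 gives two chances per score and contrast. The risk is not remote here: the arms are unmasked, outcomes are self-reported, and the Limitation section itself expects bias.

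**Working it through.** **1. The places side by side**

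| Place in the protocol article | Occasions for the scores | Deciding occasion named? |
|---|---|---|
| Outcome measures | before, immediate, 3 months after the interventions | no |
| Abstract, Methods | baseline, 3 months | only one follow-up mentioned |
| Phase 5 analysis | before, after (undated) | no |
| Phase 5 analysis, Pap smear only | 3 months from enrolment and baseline survey | not about the scores |
| Sample size | none | no |

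The 3-month point also has two origins: the interventions for the scores, and enrolment for the Pap smear. They differ by the length of the intervention, which the readable text does not give.

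**2. The plan's own figure**

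The plan calls 61 per group "adequate at an alpha of 0.05 and a power of .80, to test for a difference between the groups". It gives no means, standard deviations or occasion, so 61 cannot be rebuilt and can only be inverted. With n = 2(z₀.₉₇₅ + z₀.₈₀)²/d²:

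d = √[2 × (1.960 + 0.842)² / 61] = 0.507.

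The step to 70 recruited fits 61 × 1.15 = 70.15.

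**3. Type I error if either occasion may count (illustration)**

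For one score and one contrast, with both occasions tested two-sided at 0.05 and correlation ρ between the two test statistics:

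error = 1 − P(|Z₁| < 1.96 and |Z₂| < 1.96).

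| ρ (assumed) | error |
|---|---|
| 0 | 9.75% |
| 0.3 | 9.5% |
| 0.5 | 9.1% |
| 0.7 | 8.3% |
| 0.9 | 7.0% |

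The 0.05 comes from the sample size section. The analysis section prints 0.5, which is a separate matter.

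**4. What baseline adjustment would give (illustration)**

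With n = 61 per group and d = 0.507, the noncentrality of the unadjusted two-sample t-test is 0.507 × √(61/2) = 2.80, and its power is about 79% (80% by the normal approximation). Adjusting for a baseline score with correlation r to follow-up changes the effective difference to d/√(1 − r²). For an assumed r = 0.5 this is 0.507/0.866 = 0.586, the noncentrality is 3.24, and power is about 89%. For r = 0.3 and r = 0.7 it is about 83% and 97%.

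**The case against.** The other side has substance.

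- **The abstract may simply be condensed.** Its sentence is garbled and does not say that baseline and 3 months are the only assessments. A trial with three occasions is compatible with an abstract that names two. This stands: a reader might infer a flat three-way contradiction, or that the abstract rules out the immediate assessment, and the text does not support either.
- **Table 2 is not shown.** It may list the visits. This also stands and limits confidence. A list of visits would not by itself say which visit decides.
- **The planned tests can be run once per occasion.** That is true, so the analysis section does not exclude three occasions. But running them twice gives two unadjusted tests per score and contrast, with neither marked as primary.
- **Such detail may sit in a statistical analysis plan that is not shown.** That excuse covers the mechanics of the tests. It is weaker for the deciding occasion, which belongs to the definition of a primary outcome; the article does define these outcomes and gives the two occasions equal rank.
- **The figures are hypothetical.** No passage states that either occasion may count. The standardised difference of 0.507 is inverted from a sample size that the article links to comparing participation, not to an I-Change score. This stands, and the figures are offered as illustration only.
- **A t-test at a named occasion would already remove the ambiguity.** Correct. Baseline adjustment is an added gain in efficiency, not a condition for repairing the time point.

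**Conclusion.** The point holds in a limited form. All six primary outcomes have two post-intervention occasions of equal rank, the planned tests have one undated after, and no readable text says which occasion decides. Either score could therefore be presented as the primary result, or both tested at 0.05.

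The possible inflation, about 8.3% to 9.5% per score and contrast, rests on an assumed rule that either occasion counts and on assumed correlations of 0.7 to 0.3.

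Two stronger readings are not supported. One is that the 3-month comparison is underpowered: the documents give no effect by occasion, so fading and the power it would cost are possibilities only. The other is that every section already places the scores at 3 months: the analysis section gives that time for Pap smear completion alone, counted from enrolment.

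**What to change.** 1. Name one primary time point for the six I-Change outcomes, with its origin, and state it identically in the abstract, the outcome section and the Phase 5 analysis. Three months after the intervention is the natural choice, because the abstract and the outcome section both place the scores at 3 months. Reconcile the enrolment origin used for the Pap smear, and check Table 2 against the result.
2. Label the immediate assessment secondary.
3. Replace the undated before-and-after tests with a between-arm comparison of the 3-month score adjusted for the baseline score already collected. This can be ANCOVA, or a mixed model of the immediate and 3-month values with baseline taken into account and the arm contrast read at 3 months. Under the assumptions shown above, adjustment raises power from about 79% to about 89% at 61 per group.

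The cost is small. Neither the 3-month score nor the baseline score is a new measurement. Because recruitment opened in October 2021, the change is a documented amendment during an ongoing trial and should be dated before outcome data are compared by arm. The one loss is that a gain seen only immediately can no longer be presented as the primary result.

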### Ethical approval

The study protocol has been ethically approved by the Faculty of Medical Sciences, Tarbiat Modares University of Iran (reference number: IR.MODARES.REC.1400.049). The rights and welfare of the participants will be protected according to the Declaration of Ethical Principles for Medical Research. Data that is collected as part of the study will not be linked to any individual, personal identifiers will not be used in data storage, and confidentiality will be maintained at all levels of data management. Only members of the research team have access to data collected in the project. Plans for communicating important protocol modifications (e.g., changes to eligibility criteria, outcomes, analyses) to relevant parties (e.g., investigators, trial participants, trial registries) will be considered and the corresponding author of this research is responsible for any protocol amendments.

### Participation

The research population will include women aged 18–49 years who register interested in participating in a trial intervention. Participation in the study will be stretched to all eligible women until we reach a sample size of 210 women who provide informed consent to participate.

### Requirement

First, participants will be recruited via an online call through the virtual platforms such as Instagram pages, WhatsApp, and Telegram channel. Candidates will communicate with the trained research assistant (SK; the first author) through the phone number included in the announcement. Then, the research assistant explains the purpose of the study by phone for women who are eligible to enter the study. She will obtain contact information from potential trial participants. The assent will be sent via email or any social media messenger such as Telegram or WhatsApp. Table 1 contains a complete list of the inclusion and exclusion criteria.

**Table 1 Tab1:** Inclusion and exclusion criteria

Inclusion criteria	Exclusion criteria
Women aged 18–49 years Married (having at least one sexual relationship experience) Being the residence of North Iran during the study Tend to participate with informed consent to share information, and participate Women own a smartphone and the ability to use it Women without mental disorders, drug dependence, and addiction	Absence of more than two sessions in training sessions Having a special illness that prevents participants to take part in training sessions Woman who is not interested in the subject of the curriculum

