### Randomization

After informed consent and baseline data collection, participants in the randomized controlled trial will be randomly assigned to the intervention and control arms in a restricted randomized block design. A research identification number will be given to each woman. Then, the identified individuals who volunteered to participate in the study were randomly assigned to the experimental and control groups using a blocking method. Following simple randomization procedures, participants will be assigned to one of the three arms of the trial in a 1:1:1 ratio according to a computer-generated randomization schedule via https://www.sealedenvelope.com/simple-randomiser/v1/lists. The letter A will be considered for the intervention group1, the letter B will be considered for the intervention group2, and the letter C for the control group. The process of random allocation will be continued continuously until the sample size will be reached. Masking of participants and study staff is not possible due to the nature of the intervention (educational) and allocation ratio.

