#### Phase 5: the randomized controlled trial for effectiveness evaluation of the app-based intervention

##### Intervention description

This study is a parallel-group randomized controlled trial. Eligible participants are randomized in a 1:1:1 allocation ratio to one of three groups: two experiment groups, in which women receive the application (app) and digital book. The training contents in both experimental groups outlined preventive behaviors of CC regarding I-Change model constructs retrieved from phases one and two. In another word, group A will be called mobile app group and group B will be called the Digi booklet-group and will receive the same training content in different ways (Fig. 1).

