**Fig. 1 Fig1:**
[figure not shown]
The flow chart of the randomized controlled protocol

Each of the participants in experiment groups A and B will be required to register as a user to download the mobile-App and Digi booklet separately. The educational content will be based on the latest national and international guidelines for the prevention of CC of information (facts).

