##### Control group

Group C as the control group will receive no training content during the study. Following the ethical issue, they only will be provided with educational materials at the end of the intervention procedure. They will receive routine care, such as free health information brochures and free counseling services as needed.

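### Table 1 excludes women who miss training sessions that the Phase 5 intervention never describes; applied as written, the rule would act only after randomisation and only in the two intervention arms

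*Protocol article*

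**What the plan says.** The Requirement section presents Table 1 as the full set of eligibility criteria. Two of its three exclusion criteria depend on sessions: "Absence of more than two sessions in training sessions" and "Having a special illness that prevents participants to take part in training sessions".

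The Phase 5 intervention description speaks of "two experiment groups, in which women receive the application (app) and digital book". Groups A and B "will receive the same training content in different ways". The text after Fig. 1 adds that each participant in A and B "will be required to register as a user to download the mobile-App and Digi booklet separately". In the text available, Phase 5 gives no session, number of sessions, timetable or attendance record. The only other sessions mentioned are the focus groups on app design in Phase 4, which are not participant training.

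On control, the plan states: "Group C as the control group will receive no training content during the study". On sequence, the Randomization section states: "After informed consent and baseline data collection, participants in the randomized controlled trial will be randomly assigned to the intervention and control arms". The Outcome measures section sets the assessments "in the target and control groups before, immediately, and 3 months after the interventions".

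**The concern.** Two parts of the same document imply different things about what women in A and B are exposed to. Table 1 presupposes a course that can be attended or missed. Phase 5 describes material that a woman downloads for herself. A reader cannot tell which is being tested.

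The more serious consequence comes from where the attendance rule sits. An exclusion criterion normally acts before randomisation and equally on all arms. This one depends on behaviour after allocation, in arms that have something to attend. If it is followed, the women who engage least leave A and B, while women of the same disposition stay in C. The A versus C and B versus C comparisons, which answer the trial's main question, would no longer compare groups formed by randomisation. If poor adherers also tend to have poorer outcomes, the bias favours the intervention.

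A smaller point follows. An assessment made immediately after the intervention needs a defined end of intervention. The visible text gives none for downloaded material, and group C has no intervention to end.

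**Working it through.** **Setting the passages side by side**

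1. *Are there sessions?* Table 1 implies at least three, since more than two can be missed. The Phase 5 description and the text after Fig. 1 mention none.
2. *When can the absence criterion be met?* Only once training has started. Randomisation comes after consent and baseline data, so it can be met only after randomisation.
3. *In which arms?* Group C receives no training content, so only in A and B.
4. *What about the illness criterion?* It can be judged at entry in all arms, so it does not select by arm. It still refers to sessions that are not defined.
5. *When is the immediate assessment?* Outcome measures counts from the interventions, while the Phase 5 analysis section counts three months for Pap smear completion from enrolment and the baseline survey. Table 2, which holds the schedule, is not shown and may settle this.

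Steps 2 and 3 together give a post-randomisation exclusion that acts on A and B alone.

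**How large could the effect be?** The contradiction itself rests on no figure. The following is illustration only.

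Inputs from Sample size and power calculations: 61 per group, alpha 0.05 (two-sided, from the formula), power 0.80, 15% dropout, 70 recruited per group.

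- Plan's figure: 61 × 1.15 = 70.15 and 61 / 0.85 = 71.8. The stated 70 reproduces to within 2 women, and 3 × 70 = 210.
- The means and SDs behind the 61 are not given. Inverting the formula, the implied standardised difference is d = √(2 × (1.960 + 0.842)² / 61) ≈ 0.507.
- Women left per arm after dropout: 70 × 0.85 = 59.5.

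*Bias.* Let p be the share of an intervention arm removed by the rule. Let D be the gap in mean outcome, in SD units, between women kept (mean K) and women removed (mean R). The mean of the whole arm is (1 − p)K + pR, so the kept mean exceeds it by p(K − R) = pD. Control is unchanged, so the contrast moves by pD. The documents give neither p nor D. With p of 10%, 20% and 30% and D equal to 0.507:

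| p | Shift, pD | As share of d |
|---|---|---|
| 10% | 0.051 SD | 10% |
| 20% | 0.101 SD | 20% |
| 30% | 0.152 SD | 30% |

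If D is 0 there is no bias, and intermediate values scale in proportion.

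*Power.* With n_T = 59.5(1 − p) in the intervention arm and n_C = 59.5, power = Φ(d / √(1/n_T + 1/n_C) − 1.96). This gives 0.79 at p = 0, 0.77 at 10%, 0.74 at 20% and 0.71 at 30%. The power loss is modest. The selection matters more, because a larger sample would not cure it.

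**The case against.** The strongest reply is that the session wording is harmless. Table 1 is an eligibility list. It sets no dose, number, place or format of sessions. The words may be left over from a template, or may mean units of the downloaded content, since Phase 5 speaks of training content and the app's modules are still to be determined in Phase 4. Use logs and adherence definitions are also details that an article often leaves to the full protocol, and the assessment schedule may be fixed in Table 2.

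Much of this stands. Because of it, three stronger inferences should not be drawn:

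- *That an app effect would really be an effect of sessions.* No passage says that sessions accompany the app or booklet. If both A and B had the same sessions, A versus B would not be confounded by them.
- *That A and B get at least three contacts and C none.* A session need not be a personal contact, and the Control group section gives C routine care, with brochures and counselling as needed.
- *That the immediate assessment drifts by weeks between women or arms.* No completion time is stated, nothing ties the assessment to each woman's completion, and Table 2 cannot be seen.

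The reply does not remove the core. Whatever a session means, even a module of the app, the absence criterion is listed as an exclusion, depends on behaviour after allocation, and cannot be met in group C. That is stated text, not omitted detail.

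**Conclusion.** The point holds in a limited form. The eligibility table and the Phase 5 description contradict each other on whether training sessions are part of the exposure, and nothing in the visible text resolves it. The absence criterion, if applied as written, is a one-sided exclusion after randomisation that would bias A versus C and B versus C.

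Its size cannot be determined from the documents. Under the assumptions shown (10% to 30% of an intervention arm removed, and a gap between kept and removed women of up to 0.507 SD), the shift runs from 0 to about 0.15 SD, and power falls from 0.79 to as low as 0.71. The direction favours the intervention only if women who miss sessions have worse outcomes than those who attend, which is plausible but not stated. If the investigators never apply the criterion, no such bias arises and only the contradiction remains.

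The timing point is secondary and lapses if Table 2 already fixes a common date.

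**What to change.** 1. Reconcile Table 1 with the Intervention description and Control group sections: state whether training sessions exist, what they are and in which arms.
2. Remove the attendance criterion from the exclusion list. Reword the illness criterion so that it matches the actual delivery and is judged before randomisation in all arms.
3. Record missed sessions, or non-use of the material, as adherence, for example from app and booklet registration or use records. Follow up every randomised woman and analyse her in her assigned arm.
4. Set the immediate assessment at one fixed time from randomisation, identical in all three arms, unless Table 2 already does so.
5. If sessions are in fact held, describe them equally for A and B, and word the A versus C and B versus C conclusions as the effect of sessions plus material.
6. The Trial status section says that recruitment is under way. If women have already been excluded for absence, report the number by arm and seek their outcome data.

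The cost is an amendment to Table 1 and short edits to the intervention and outcome sections. Registration is already required for the download, so adherence recording should add little. No change to the sample size is needed on this account.
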